## Discussion

Considering today’s call for more patient participation in medical decision-making, the convenience of taking up information and drawing blood close to home, paired with customized advice from the very first consultation, might appeal to patients. Replacing the face-to-face intake consultation with a genetic counselor by a home informational package of telephone, written and digital information might speed up the diagnostic process of hereditary breast cancer and reduce extraneous information. For example, this would allow patients to go over this information at their own convenience and in their own homes. It could possibly reduce travel efforts to a hospital as well as time conflicts with breast cancer therapy.

However, there are certain downsides compared to traditional genetic testing. All patients with breast cancer referred to clinical genetics by their treating physician are eligible for the DNA-direct procedure. This means that even those patients who would not normally fulfill criteria for *BRCA1/2* testing are now able to have their blood drawn for DNA-testing, regardless of those criteria. In the DNA-intake procedure, patients who do not fulfill the aforementioned criteria will not be offered further DNA-testing. This may lead to a selection bias. Our intention is to compare DNA-direct to current practice: adhering to these criteria is the current practice and must be reflected in the DNA-intake procedure.

Additionally, genetic counselors must adjust their counseling styles to the disclosure of the DNA-results being the first order of business, without having built up a counselor-patient relationship beforehand. New information might come forward following result disclosure, leading to ad-hoc modification of screening advice. For this reason, as well as to avoid intercounselor variation, we have selected five genetic counselors with many years of experience in oncogenetic counseling to see all patients participating in this study (both DNA-direct and DNA-intake).

In conclusion, the aim of our study is to determine whether DNA-direct is an acceptable procedure for *BRCA1/2* testing, in order to provide customized care to patients with breast cancer and remove unnecessary waiting times within the diagnostic process, cutting down on the long period of uncertainty that patients are currently faced with.

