## Methods/design

### Design

The study examines the effect of the DNA-direct procedure on the experience and psychological distress of patients with breast cancer as well as several secondary outcome measures, including waiting and processing times, as compared to the current DNA-intake procedure. Two groups will be compared: the intervention group, who choose to undergo the DNA-direct procedure, and the control group, who will receive care as usual (DNA-intake procedure). Participants may choose freely between the DNA-direct versus DNA-intake procedures. This study is not randomized due to the wish to evaluate whether there is indeed a desire for the proposed DNA-direct procedure amongst patients with breast cancer, and to evaluate the reasons stated for preferring one procedure over the other.

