### Study sample

All female patients previously or currently diagnosed with breast cancer and referred to the department of Clinical Genetics of the Radboud University Nijmegen Medical Centre from August 9th 2011 are eligible for inclusion. Recruitment will continue until the desired total of 150 participants is reached. Patients who have problems reading Dutch text, problems with family communication or problems of psychological/psychiatric nature (including current use of related medication) will be excluded.

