#### Experiences with genetic counseling (follow-up)

##### Decisional conflict

The difficulty of decision-making, in this study defined as whether or not to undergo genetic testing, is assessed using the traditional format of the Decisional Conflict Scale; 1 item (“I expect to stick to my decision”) is left out as it is not applicable to DNA-testing [57-59]. 15 items scored 0,1,2,3,4 from 0 ‘strongly agree’ to 4 ‘strongly disagree’ remained, including “I am satisfied with my decision” which is also used separately for overall satisfaction. Scores are summed, divided by 15 and multiplied by 25, resulting in a range from 0 to 100. Scores below 25 are considered as ‘no decisional conflict’, between 25 and 37.5 as ‘moderate conflict’ and exceeding 37.5 as ‘severe conflict’. The DCS has good internal consistency exceeding 0.78 [57-59].

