#### Other measures

Waiting and processing times, as well as family pedigree characteristics, are also gathered.

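### Access to DNA-testing differs by group for patients who fail the testing criteria, and the planned whole-group comparison has no supporting analysis by criteria status

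*Protocol article*

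**What the plan says.** Entry does not depend on the testing criteria. The Study sample section admits "All female patients previously or currently diagnosed with breast cancer and referred to the department of Clinical Genetics", subject to exclusions for language, family communication and psychological problems. The Design section adds that "Participants may choose freely between the DNA-direct versus DNA-intake procedures".

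The Discussion then describes unequal access to the test. Under DNA-direct, patients who would not normally qualify "are now able to have their blood drawn for DNA-testing, regardless of those criteria". For the control group it says "In the DNA-intake procedure, patients who do not fulfill the aforementioned criteria will not be offered further DNA-testing". It concedes "This may lead to a selection bias" and keeps the arrangement on purpose, because "adhering to these criteria is the current practice and must be reflected in the DNA-intake procedure".

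Under Study outcomes, the second questionnaire is due once counseling, testing or both have ended, so DNA-intake patients who were never tested also supply follow-up data. Decisional conflict, listed among the primary outcomes, concerns the testing decision: "in this study defined as whether or not to undergo genetic testing". Under Other measures, "Waiting and processing times, as well as family pedigree characteristics, are also gathered".

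The Statistical analysis section compares intervention with control as whole groups. Its regression model adjusts for the baseline result and for whatever proves significant in univariate analyses. It names no stratum, restricted set or sensitivity analysis by criteria or tested status.

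**The concern.** The hypothesis in the Background is about a procedure: replacing the intake consultation should not raise distress, should leave satisfaction equal and should shorten the process. The planned contrast changes two things at once, the format of pre-test information and access to the test.

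The article's own premises make the second change relevant. The Background reports that distress rises for a time after BRCA1/2 testing and later subsides, and argues that the wait for a result is itself stressful. A DNA-intake patient who fails the criteria goes through neither, yet her score counts in the control mean. Her pathway also has no laboratory phase, which shortens the control group's average time.

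For decisional conflict the difficulty is one of meaning as well as bias: a patient who was offered no test has no testing decision to score. At stake is whether a difference, or the absence of one, can be read as an effect of dropping the intake consultation.

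**Working it through.** **Which patients differ**

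| | DNA-direct | DNA-intake |
|---|---|---|
| Meets criteria | can be tested | can be tested |
| Fails criteria | can be tested | not offered a test |

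Only the first row compares the procedures with equal access. In the second row access is fixed by group, so a covariate for criteria status cannot by itself separate the effect of the procedure from the effect of being tested.

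**What 150 patients can detect.** The Sample size calculation section gives 80% power, two-sided 0.05, ratios from 50:50 to 20:80 and a total of 150, but no effect size or SD. The 150 therefore cannot be reproduced, only inverted. With SE = √(1/n₁ + 1/n₂) in SD units, the detectable difference is (1.960 + 0.842) × SE:

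- 75:75: 2.802 × 0.163 = 0.46 SD
- 30:120: 2.802 × 0.204 = 0.57 SD

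**Size of the bias (all inputs assumed).** Let a share f of each group fail the criteria, let being tested shift their outcome by D SD, and let the procedure itself have no effect. DNA-direct minus DNA-intake is then f × D. The chance that a two-sided test rejects is 1 − Φ(1.960 − fD/SE) + Φ(−1.960 − fD/SE). For f = 20% and D = 0.5 at 75:75, fD/SE = 0.10/0.163 = 0.61, which gives 0.094.

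| f | D | Bias (SD) | Rejection, 75:75 | Rejection, 30:120 |
|---|---|---|---|---|
| 10% | 0.5 | 0.05 | 0.061 | 0.057 |
| 20% | 0.5 | 0.10 | 0.094 | 0.078 |
| 30% | 0.5 | 0.15 | 0.151 | 0.114 |
| 30% | 0.8 | 0.24 | 0.312 | 0.217 |

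Without bias the figure would be 0.05.

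**Time (assumed figures).** If tested DNA-intake patients take 16 weeks and untested ones 6, a 30% untested share gives a control mean of 0.7 × 16 + 0.3 × 6 = 13 weeks. Three weeks of any DNA-direct saving would be hidden.

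**Cost of restricting to criteria-meeting patients.** Power for the effect that 150 patients detect at 80% becomes Φ(2.802 × √(1 − f) − 1.960).

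| f | Patients left | Power | Detectable, 50:50 | Detectable, 20:80 |
|---|---|---|---|---|
| 10% | 135 | 76% | 0.48 SD | 0.60 SD |
| 20% | 120 | 71% | 0.51 SD | 0.64 SD |
| 30% | 105 | 65% | 0.55 SD | 0.68 SD |

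**The case against.** The strongest reply is that the asymmetry is disclosed and intended. The article sets out to compare DNA-direct with current practice, and applying the criteria is part of current practice. For that question the whole-group contrast is the right one. This stands, and it is why the all-comers comparison should stay. It does not isolate the effect of replacing the intake consultation, and it does not give untested patients a testing decision to rate.

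Second, a journal article condenses its plan, and a subgroup or sensitivity analysis may be set out in a document not shown. The article also expects to correct for confounders not yet known, and pedigree variables could enter the model if univariately significant. This stands in part. That route depends on the data, however, and even if criteria status entered the model, adjustment alone would not suffice.

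Third, the size is unknown. A bias of 0.05 to 0.10 SD is well below the 0.46 to 0.57 SD that the study can detect. This stands.

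A reader might also infer more than the documents support:

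- That untested DNA-intake patients had no waiting period. They still wait for their intake consultation.
- That patients choose DNA-direct to get round the criteria. The Recruitment section describes a call explaining two formats and checking exclusions; nothing says that patients are told of the difference in access.
- That the time comparison is biased in favour of DNA-direct. A shorter pathway for untested controls works against it.

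**Conclusion.** The point holds as a limit on interpretation. The contrast as planned estimates the whole DNA-direct pathway, including wider test access, against current practice. Read as the effect of replacing the intake consultation, it is confounded with access to testing for distress, decisional conflict and time. It would go too far to call the whole-group analysis invalid, or to say that any observed difference must come from test access.

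The size cannot be computed, because the documents give neither the share failing the criteria nor the difference that testing makes. Under the assumptions above the bias is small at a 10% share. It could become material at 20-30%, more so if testing shifts the outcome strongly. The calculation also assumes the same failing share in both groups; with free choice the shares may differ, which would add a difference in case mix. The direction for distress is not fixed by the documents. For processing time the tendency is to conceal a saving. The Decisional Conflict Scale problem does not depend on these assumptions: it arises for every DNA-intake patient who completes the scale without having been offered a test.

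**What to change.** 1. Keep the all-comers comparison, labelled as the current-practice analysis.
2. Write down the testing criteria, which the article mentions but does not list. Classify every participant in both groups as meeting or failing them, by one rule applied to the pedigree and family-history data, by someone unaware of the group.
3. Pre-specify a supporting comparison of distress, waiting and processing time, and decisional conflict among criteria-meeting patients in both groups. Membership should depend on the criteria and not on uptake, so that qualifying patients who decline the test remain.
4. Make the between-group Decisional Conflict Scale comparison only in that set. Restricting it to patients offered testing would set all DNA-direct patients against criteria-meeting DNA-intake patients and recreate the imbalance.
5. Report the number failing the criteria in each group, so that readers can judge the likely size of the bias.

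The change needs one derived variable and one more analysis set; pedigree data are already gathered. The price is a smaller set with wider confidence intervals, as tabulated above. Some misclassification is also possible, because DNA-direct patients give family history on a mailed form and the Discussion expects new information to emerge after disclosure.

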Therefore, this study offers patients with breast cancer the choice of replacing the initial face-to-face consultation prior to DNA-testing (usual care DNA-intake procedure) by a home information package including telephone, written and digital information consisting of a website and educational movie (DNA-direct procedure). DNA-testing will thus be performed prior to genetic counseling, contrary to current practice. At the first face-to-face contact, counselors will be able to disclose DNA-results and customized advice to patients. This eliminates extraneous information which is not applicable to the individual patient, and provides patients with the information they desire in a quick and patient-centric manner.

The aim of this intervention study is to compare this new DNA-direct procedure to current practice (DNA-intake procedure). The effects of the DNA-direct procedure on the experience and psychosocial distress on patients with breast cancer, as well as the speed and quality of genetic advice, will be evaluated. The hypothesis is that undergoing the DNA-direct procedure does not lead to increased levels of psychosocial distress as compared to the usual care DNA-intake procedure, with equal levels of patient satisfaction plus shorter waiting and processing times. A trend similar to traditional *BRCA1/2* testing – a short term increase in distress, falling back to pre-testing levels over time [33-39] – is expected in the DNA-direct procedure. This would make DNA-direct an acceptable procedure for patients with breast cancer undergoing genetic testing, with the goal of more customized care, and a shorter period of uncertainty. Moreover, it would facilitate taking genetic advice into account for the treatment and follow-up of breast cancer.

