### Intervention

Patients who choose the DNA-direct procedure, receive a home informational package including an informational letter, a link to a website including a short educational movie about hereditary breast cancer and DNA-testing. Also included are two EDTA blood vials with informed consent and family history forms. Patients are instructed to call their family doctor assistant to ask where to have their blood drawn, then return the vials plus signed forms in the appropriate return package. An appointment for a personal consultation to disclose results is set 8 weeks after DNA-testing has commenced.

All patients (whether they choose DNA-direct or DNA-intake) are seen by one of five selected genetic counselors, each of whom has extensive experience in genetic counseling for hereditary cancer. These counselors have had multiple meetings in order to structure the DNA-direct consultations as follows: If no mutation is found, further screening advice is formulated based on familial risk scores: FHAT [43], Myriad [44] and Claus/van Asperen [45,46]. Further evaluation of family history and features of other hereditary cancer syndromes may be required. In the case of a pathogenic *BRCA1* or *BRCA2* mutation, this result is disclosed immediately, first allowing the patient to react, followed by an explanation of the consequences, including prevention measures and family evaluation. If considered necessary, a second consultation is offered for further genetic counseling. All confirmed *BRCA1/2* carriers will be approached by a social worker to extend psychosocial support if needed, as in usual care.

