### Statistical analysis

To compare general characteristics, baseline and follow-up results between the intervention versus control group, the unpaired *t*-test will be used for continuous variables, Mann–Whitney *U* test for non-parametric variables and chi-square test for dichotomous variables. For the comparison of baseline versus follow-up results within each group, the paired *t*-test will be used for continuous, Wilcoxon test for non-parametric and McNemar’s test for dichotomous variables. Multivariate analysis will consist of a regression model using the follow-up results as outcome (dependent) variables, to be compared between the intervention versus control groups as independent variables, with the baseline results as covariates supplemented by variables that were found to be statistically significant in previous univariate analyses. The probability level for statistical significance testing is set at 0.05 (two-tailed). The SPSS 18.0 statistical package will be used to analyze the data.

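### DNA-direct drops the intake visit and also waives the BRCA1/2 testing criteria, so the planned whole-group comparison cannot isolate the effect of replacing the intake consultation

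*Protocol article*

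**What the plan says.** The Background of the protocol article describes the intervention as a substitution of one element: "this study offers patients with breast cancer the choice of replacing the initial face-to-face consultation prior to DNA-testing". The hypothesis there is that DNA-direct "does not lead to increased levels of psychosocial distress as compared to the usual care DNA-intake procedure", with equal satisfaction and shorter times.

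The Discussion then describes who can be tested. For the new procedure: "All patients with breast cancer referred to clinical genetics by their treating physician are eligible for the DNA-direct procedure". Women who would not normally qualify "are now able to have their blood drawn for DNA-testing, regardless of those criteria". For usual care: "In the DNA-intake procedure, patients who do not fulfill the aforementioned criteria will not be offered further DNA-testing". The authors acknowledge that this may cause selection bias, and keep the criteria in DNA-intake because they are current practice.

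Under Intervention, the DNA-direct visit is a result visit: "An appointment for a personal consultation to disclose results is set 8 weeks after DNA-testing has commenced". Under Study outcomes, the second questionnaire follows the end of counseling, testing or both, so untested women answer it too.

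Under Statistical analysis, the groups are compared by univariate tests, and then: "Multivariate analysis will consist of a regression model using the follow-up results as outcome (dependent) variables". The covariates are the baseline results plus whatever proved significant univariately. Neither testing criteria nor testing status is mentioned.

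**The concern.** Two things change between the groups: the intake visit and access to a test. At follow-up, women who complete DNA-direct have received a DNA result. Part of the DNA-intake group has instead learned that no test will be offered.

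The outcomes are likely to respond to this. The Background itself says that distress rises for a time after BRCA1/2 testing and then settles, so on the protocol's own premise testing moves a primary outcome. The Decisional Conflict Scale is defined here around the decision to be tested, a decision that DNA-intake women outside the criteria are not given. Satisfaction items ask whether the woman would choose testing again.

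At stake is the inference. A finding of no difference could be read as showing that the intake visit can be dropped without harm, although a testing effect in the opposite direction may have masked an increase in distress. A difference could equally be blamed on the missing visit when it comes from wider access to testing.

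The stated model does not address this. Baseline questionnaire scores cannot remove a difference that arises after baseline. Criteria status enters only if a significance screen happens to select it. Even then a main effect is not enough, because access to testing differs between the groups only among women outside the criteria.

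**Working it through.** **1. The plan's own figure.** The Sample size calculation gives N = 150, 80% power, two-sided 0.05 and group ratios from 50:50 to 20:80. It states no effect size or SD, so 150 can only be solved backwards. By the normal approximation, d = (1.960 + 0.842) × √(1/n₁ + 1/n₂):

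- 75/75: 2.802 × √(2/75) = 0.457
- 30/120: 2.802 × √(1/30 + 1/120) = 0.572

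The noncentral t gives 0.460 and 0.576. The detectable difference is therefore about 0.46 to 0.58 SD, and 150 is neither confirmed nor refuted.

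**2. Distortion if dropping the intake has no effect.** Let q be the share of women outside the criteria, assumed equal in both groups, and t the shift in follow-up score (in SD) caused by testing and disclosure in such women. Women who meet the criteria are taken as tested in both groups. Women outside them are tested only in DNA-direct, so the spurious contrast is q × t. Neither q nor t is in the document; both are assumptions. The last two columns give the chance of p < 0.05 (normal approximation).

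| q | t | q × t (SD) | 75/75 | 30/120 |
|---|---|---|---|---|
| 10% | 0.3 | 0.03 | 5% | 5% |
| 20% | 0.3 | 0.06 | 7% | 6% |
| 20% | 0.5 | 0.10 | 9% | 8% |
| 30% | 0.5 | 0.15 | 15% | 11% |
| 40% | 0.5 | 0.20 | 23% | 17% |

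The largest value, 0.20 SD, is 0.20/0.46 = 43% of the detectable difference at 75/75 and 0.20/0.58 = 34% at 30/120.

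**3. The sign can reverse.** Suppose women tested outside the criteria mostly get a negative result and feel relief r. Assume 2% of them are carriers, with a rise of 1 SD. Their mean shift is 0.02 × 1 + 0.98 × r.

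- r = −0.2: −0.176; at q = 20% the contrast is −0.04 SD
- r = −0.5: −0.470; at q = 40% the contrast is −0.19 SD

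The carrier share, the 1 SD and r are again assumptions.

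**4. Precision of a criteria-met comparison.** If 30% fall outside the criteria in both groups, 150 × 0.70 = 105 women remain. The detectable difference (noncentral t) is 0.55 SD at 52/53 and 0.69 SD at 21/84.

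**The case against.** The strongest reply is that the declared aim is DNA-direct against current practice. The Background and the Discussion both say so, and open access to testing is part of the DNA-direct package. On that reading the all-patient contrast answers the question, and making criteria-met women the sole deciding population would substitute another estimand and lose precision. This stands: the all-patient comparison should be kept. It does not license the further reading that the intake visit itself can be dispensed with, which the description of the intervention invites.

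A reader might infer that every DNA-direct woman is tested and every comparison with DNA-intake is therefore invalid. The text does not support that. It says women are able to have blood drawn; someone could choose DNA-direct and not return the vials. Only those who complete the procedure are tested by design.

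A reader might also infer a serious bias of known size. The documents give neither the share outside the criteria nor any testing effect, and free choice may make that share differ between groups. If few women miss the criteria, the distortion is negligible.

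The authors disclose the difference, and supplementary analyses are often left to a fuller plan. Both points are fair and reduce the severity. But the article states the model, and that model does not respond to the problem its Discussion raises.

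Finally, the testing criteria are not defined in the article, and family history is collected differently: home forms in DNA-direct, a face-to-face intake in DNA-intake. Classification may therefore be less complete or less even than hoped. This too stands, and is why one rule must apply to both groups.

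**Conclusion.** The point holds as a limit on interpretation and a worthwhile improvement; it does not invalidate the planned comparison. The all-patient contrast describes the package against usual care, subject to self-selection. It cannot separate dropping the intake from widening access to testing. The distortion has unknown size and sign: about 0.06-0.20 SD in absolute size for assumed shares of 20-40% and assumed testing effects of 0.3-0.5 SD, with the reverse sign possible if relief after negative results dominates. It is close to nil if few women fall outside the criteria. The tempting conclusion that a criteria-met comparison would isolate the effect of the intake visit goes too far, because women choose their procedure freely and that confounding remains.

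**What to change.** Classify every participant in both groups as meeting or not meeting the usual BRCA1/2 testing criteria. Apply the same written rule in both groups, blind to questionnaire scores, using the family history forms, age, cancer status and pedigree data ("Waiting and processing times, as well as family pedigree characteristics, are also gathered"). Report how many cannot be classified, by group.

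Keep the all-patient comparison and label it as the package against usual care. Prespecify beside it a criteria-met comparison for distress, satisfaction and decisional conflict. This can be a restriction to criteria-met women, or a model with criteria status and its interaction with procedure, read at criteria met. State that any conclusion about replacing the intake consultation rests on this second contrast. Describe DNA-direct women outside the criteria and untested DNA-intake women separately.

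The cost is one derived variable and some analysis wording. The data sources are already planned, provided they suffice to apply the criteria. The criteria-met contrast is less precise (0.55-0.69 SD detectable if 30% are outside, against 0.46-0.58 SD for all 150). Keeping the original detectable difference at that share would take 150/0.70, about 215 women. Self-selection still has to be handled by covariate adjustment and acknowledged.
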